**Methods:**

The PERYTON-study is a prospective multicentre open phase III randomised controlled trial. We aim to include 538 participants (269 participants per treatment arm) with a BCR after prostatectomy, a PSA-value of < 1.0 ng/mL and a recent negative PSMA PET/CT scan. Participants will be randomised in a 1:1 ratio between the conventional fractionated treatment arm (35 × 2 Gy) and the experimental hypofractionated treatment arm (20 × 3 Gy). The primary endpoint is the 5-year progression-free survival after treatment. The secondary endpoints include toxicity, quality of life and disease specific survival.

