**Figure Fig1:**
[figure not shown]
**Fig. 1** The design of the PERYTON-trial

Participating centres are radiotherapy treatment centres in the Netherlands (updated list available on ClinicalTrials.gov).

All eligible participants will be randomly assigned (1:1) to receive:Current standard: conventional sEBRT, 35 × 2 Gy, biologically equivalent dose: 70 Gy.Experimental arm: hypofractionated sEBRT, 20 × 3 Gy, biologically equivalent dose: 78 Gy.

Participants will be stratified by PSA level (≤0.2 ng/mL vs > 0.2- ≤0.5 ng/mL vs > 0.5- < 1.0 ng/mL) and local recurrence on the PSMA PET/CT (presence versus absence).

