### Follow-up evaluation

Participants will be followed according to the time schedule in Table 3.

**Table 3 Tab3:** Summary of the follow-up in the first 5 years after RT

Required investigation	Inclusion (within 4 wk. prior to randomisation)	During treatment		Follow-up							
		4 wks	7 wks	1.5 m after RT	3 m after RT	6 m after RT	9 m after RT	12 m after RT	18 m after RT	24 m after RT	Every 12 m (up to 60 m)
Eligibility check	X										
Informed consent	X										
Characteristics	X										
Medical history / medication list	X			X	X	X	X	X	X	X	X
WHO performance status	X			X		X		X	X	X	X
pT-stage and GSS	X										
PSA	X			X	X	X	X	X	X	X	X
Testosterone	X							X		X	X
PSMA/PET CT	X										
Radiotherapy treatment planning		X									
Survival / progression status				X	X	X	X	X	X	X	X
Surveys											
CTCAE v5	X	X^a^		X	X	X	X	X	X	X	X
RTOG-EORTC Toxicity	X	X^a^		X	X	X	X	X	X	X	X
EORTC-QLQ-PR25	X				X	X	X	X	X	X	X
EORTC-QLQ-C30	X					X	X	X	X	X	X
SAE				X	X	X	X	X	X	X	X

^a^Have to be completed at the end of radiotherapy (4 weeks in the experimental arm and 7 weeks in the standard arm)

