### Statistical analysis

The incidence of progression-free survival will be compared between the two treatment arms using Cox proportional hazards regression analysis to calculate hazard ratios and 95% confidence intervals. Acute and late toxicity rates will be summarized in terms of the proportion of participants in each arm. Log-binominal regression will be used to compare the individual highest grade of acute toxicity and the individual highest grade of late toxicity between both treatment arms. Relative risks will be calculated with 95% confidence intervals. For the analysis of QoL data, a comparison of the change in QoL from baseline level and at different time points will be performed between both treatment arms. The statistical analysis of QoL will be performed by a random effects linear regression model. Stratified randomisation will be taken into account in all analyses by adding the stratification variables to the respective regression models.

In sensitivity analyses, we will repeat all analyses, but with adjustment for potentially prognostic factors (age, pre-operative tumour stage, PSA level, time between radical prostatectomy and biochemical relapse, and comorbidity) or confounding factors (treatment centre).

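### The QoL analysis names change from baseline and two covariate lists but not baseline QoL; adjusting for it would gain precision at no cost

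*Protocol article*

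**What the plan says.** All of the analysis wording is in the Statistical analysis section of the protocol article.

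- **What is compared:** "a comparison of the change in QoL from baseline level and at different time points will be performed between both treatment arms".
- **Model:** "The statistical analysis of QoL will be performed by a random effects linear regression model".
- **Terms added to every model:** "Stratified randomisation will be taken into account in all analyses by adding the stratification variables to the respective regression models". Under Study design these variables are PSA level in three classes and presence or absence of local recurrence on PSMA PET/CT.
- **Sensitivity covariates, for all analyses:** "age, pre-operative tumour stage, PSA level, time between radical prostatectomy and biochemical relapse, and comorbidity", and treatment centre as a possible confounder.

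Table 3 (Follow-up evaluation) marks QLQ-C30 and QLQ-PR25 in the column headed "Inclusion (within 4 wk. prior to randomisation" and at repeated visits up to 60 months. A pre-randomisation score is therefore planned for each scale. QoL is a secondary endpoint (Abstract, Methods: "The secondary endpoints include toxicity, quality of life and disease specific survival") and has no sample size calculation of its own.

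**The concern.** The article states the comparison as change from baseline and names two sets of covariates, chosen mainly for an oncological outcome. The baseline value of the same scale, usually the strongest predictor of a later QoL score, is in neither set.

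A change score subtracts the whole baseline value, as if a one-point difference at baseline carried forward as one point at follow-up. When the correlation between baseline and follow-up is below 1, that over-corrects. The result is extra variance, and an arm that starts lower by chance tends to show more improvement through regression to the mean.

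At stake are the width of the confidence intervals for the QoL scales and how far a chance baseline difference moves the reported contrast. QoL is one of the outcomes by which the tolerability of the hypofractionated schedule will be judged, and the trial was not sized for it.

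**Working it through.** **Plan's own figures.** None is given for QoL. The numbers per arm come from Sample size considerations, which concerns the primary endpoint: 235 evaluable and 269 recruited. These reproduce closely. With HR = ln(0.74)/ln(0.62) = 0.630, two-sided 5% and 81% power, 151 events are needed, and 151/(0.38+0.26) = 236 per arm. For dropout, 235/0.88 = 267.05, so 268. They serve here only as sample sizes.

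**Assumptions.** Scores are in SD units, with the same SD at baseline and follow-up. The correlation rho is not in the document, so a range is shown.

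**Step 1: variance at one visit.** Per-participant variance is 2(1-rho) for the change score and 1-rho² after baseline adjustment. The ratio is (1-rho²)/[2(1-rho)] = (1+rho)/2, and its inverse gives the extra participants that the change score needs for equal precision. The detectable difference (80% power, two-sided 5%, 235 per arm) is (1.960+0.842) × √(2V/235), with V the relevant variance.

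| rho | Change score V | Adjusted V | Ratio | Extra participants | Detectable difference, change vs adjusted (SD) |
|---|---|---|---|---|---|
| 0.3 | 1.40 | 0.91 | 0.65 | 54% | 0.306 vs 0.247 |
| 0.4 | 1.20 | 0.84 | 0.70 | 43% | 0.283 vs 0.237 |
| 0.5 | 1.00 | 0.75 | 0.75 | 33% | 0.258 vs 0.224 |
| 0.7 | 0.60 | 0.51 | 0.85 | 18% | 0.200 vs 0.185 |
| 0.9 | 0.20 | 0.19 | 0.95 | 5% | 0.116 vs 0.113 |

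For an assumed true difference of 0.25 SD and rho 0.5, power is 77% with the change score and 88% with adjustment.

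**Step 2: several visits.** Take the mean of four follow-up visits with every pairwise correlation 0.5. The variance of that mean is 0.5/4 + 0.5 = 0.625. Change score: 0.625 + 1 - 2(0.5) = 0.625. Adjusted: 0.625 - 0.5² = 0.375. The ratio is 0.60, so under this correlation pattern the loss is larger than at a single visit.

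**Step 3: effect of a chance imbalance.** With no treatment effect and an observed baseline difference d, the expected follow-up difference is rho·d, so the expected change-score contrast is rho·d - d = -(1-rho)d. With 269 per arm, the SE of d is √(2/269) = 0.086 SD, and the 95% limit is 1.96 × 0.086 = 0.17 SD. The shift is then 0.5 × 0.17 = 0.085 SD at rho 0.5, 0.10 SD at rho 0.4 and 0.05 SD at rho 0.7.

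**Step 4: simulation check** (4,000 trials, 235 per arm, rho 0.5, no true effect).

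- Variance ratio: 0.76 for one visit (theory 0.75) and 0.60 for the mean of four.
- Slope of the change-score contrast on the baseline difference: -0.48 for one visit and -0.50 for the mean of four. For the adjusted contrast it was about 0.
- Mean estimates: -0.001 (change score) and 0.000 (adjusted), so neither is biased over randomisation.

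**The case against.** The strongest reply is that the article does not exclude baseline QoL. The first sentence on QoL says what is compared between arms, not what the dependent variable is. A random effects model with baseline in the outcome vector also yields arm differences in change from baseline. The sentence on "adding the stratification variables to the respective regression models" explains how stratification is handled and need not list every term; visit and arm-by-visit terms are not named either. The sensitivity list is shared by all analyses, so a QoL-specific covariate would hardly appear there. Full model terms commonly stand in an SAP, which is not shown.

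Much of this stands. Three stronger readings are tempting, and the document supports none of them:

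- A reader might infer that the plan has settled on an unadjusted change score. The text leaves open whether baseline is subtracted, modelled as a response or entered as a covariate.
- A reader might infer that the QoL comparison is biased. Under 1:1 randomisation it is not; a chance imbalance only shifts the estimate conditional on that imbalance.
- A reader might extend the point to toxicity. Toxicity has its own log-binomial analysis, which this does not touch.

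The reply does not remove the point. The article chose to state the form of the comparison and its covariates, and an analyst following that wording literally would fit the less precise model. Modelling baseline as a response helps only if the arm means are constrained equal at baseline; with arm-specific baseline means it behaves like the change score.

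**Conclusion.** The point holds as a minor, conditional improvement. If the QoL model is run on change scores with only the named covariates, the arm comparison remains unbiased over randomisation, but its single-visit variance is 1.18 to 1.43 times that of a baseline-adjusted analysis for rho of 0.7 down to 0.4. At rho 0.9 the factor is only 1.05. At rho 0.5, a 95%-limit chance imbalance would move the observed contrast by about 0.085 SD in the direction opposite to the imbalance.

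These sizes rest on an assumed rho, equal SDs at baseline and follow-up and, for the ratio, a single visit. The primary endpoint and its sample size are unaffected.

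**What to change.** State how baseline QoL enters the random effects model, in one of two ways:

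- include the baseline score of each scale as a covariate, with arm-by-visit terms; or
- model baseline as a response alongside the follow-up visits, with the arm means constrained equal at baseline.

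Arm differences in change from baseline can be reported from either model. With baseline as a covariate, the arm difference is the same whether the outcome is written as the follow-up score or as the change. The stratification variables stay in the model as planned.

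The cost is one sentence in the analysis plan, with no new data, visits or participants. It should be written before QoL data are compared by arm, so that the choice cannot depend on the results. If the SAP already says this, nothing more is needed.

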### Interim analysis

Dose-limiting constraints for rectum and bladder will be used (Table 2) and a QA process is mandatory before the start of inclusion in the participating centres. Toxicity is expected to be equivalent in both arms. Nevertheless, a slight increase in acute toxicity in the experimental arm might be expected due to the short overall treatment time [29]. Therefore, we will perform an interim analysis after the inclusion of 25% of the estimated number of participants (135 participants) to identify any early signs of excessive (unexpected) acute toxicity. Grade 3 CTCAE acute toxicity will be used for this interim analysis; i.e., > 5% difference in grade 3 toxicity between the experimental and control arm. If this acute toxicity difference exceeds 5%, a formal interim analysis will be performed with a nominal *p* value < 0.001 according to the Haybittle-Peto alpha spending function, to indicate statistical significance [30]. The interim analysis will be performed by an independent statistician, and the results will be shared with the principal investigators who will judge after informing the ethical committee whether continuation of the study is safe.

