### Secondary endpoints

Acute grade ≥ 2 gastrointestinal (GI) and genitourinary (GU) toxicities measured 3 months after treatment using both physician-reported score (Common Terminology Criteria for Adverse Events (CTCAE), version 5.0) and patient-reported questionnaires (RTOG Acute Radiation Morbidity Criteria using adapted RTOG/EORTC acute Radiation Morbidity questionnaires);3- and 5-year late grade ≥ 2 GI and GU toxicities, measured using both physician-reported score (CTCAE version 5.0 criteria) and patient-reported questionnaires (RTOG/EORTC criteria);QoL, using the European Organization for Research and Treatment of Cancer (EORTC) QoL thirty item score questionnaires (QLQ-C30) for health-related QoL and the EORTC QoL prostate carcinoma module (QLQ-PR25) is used;Metastasis-free survival: Randomisation date to the date of metastases reported by imaging;PCa-specific mortality;Overall survival at 5 years from date of randomisation.

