### Sample size considerations

A systematic review and meta-analysis reported that each additional Gy in the conventional sEBRT-arm is possibly associated with a 2% higher bPFS, independent of other factors. These results imply that our biological dose escalated effect with hypofractionation will result in 16% higher bPFS (8 Gy × 2% per Gy). However, this meta-analysis did not include series using a radiotherapy dose above 70 Gy. In higher dose series as proposed in this study, the relative benefit may be lower and consequently an expected benefit of 16% may be too optimistic. Therefore, a conservative 12% higher 5-year bPFS in the experimental arm of 20 fractions of 3 Gy compared to the conventional sEBRT schedule of 35 fractions of 2 Gy (70 Gy) has been chosen. This estimated benefit of 12% is also supported by a meta-analysis including conventional and hypofractionated regimens addressing the influence of fraction size and the total dose effect on bPFS and toxicity [28].

The results of the GETUG-AFU 16 trial showed a 5-year bPFS of 62% with the conventional fractionated radiotherapy protocol [26]. We used this percentage (62%) for the 5-year bPFS in our conventional sEBRT treatment arm. Following the above mentioned literature, we hypothesize that with the experimental regimen the bPFS can be improved from 62 to 74%. Using an alpha of 5% and a study power of 81%, the required sample size is 235 participants per treatment arm. Assuming a dropout of 12%, we need to recruit 269 participants per treatment arm: 538 in total.

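### The interim acute-toxicity trigger is worded as grade 3 only; read literally, it leaves grade 4 and 5 events out of the comparison that opens the formal test

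*Protocol article*

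**What the plan says.** The Interim analysis section plans one safety look, "after the inclusion of 25% of the estimated number of participants (135 participants"), whose purpose is "to identify any early signs of excessive (unexpected) acute toxicity". The variable is named first as "Grade 3 CTCAE acute toxicity will be used for this interim analysis" and then as a "> 5% difference in grade 3 toxicity between the experimental and control arm". The formal test is conditional on that difference: "If this acute toxicity difference exceeds 5%, a formal interim analysis will be performed with a nominal" p value below 0.001.

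Three other places bear on the reading:

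- Secondary endpoints uses the ≥ sign where a grade and everything above it is meant: "Acute grade ≥ 2 gastrointestinal (GI) and genitourinary (GU) toxicities measured 3 months after treatment". The late toxicity endpoint is written the same way.
- Statistical analysis compares the arms on each participant's highest grade of acute and of late toxicity. The Interim analysis section states no counting rule.
- Table 3 schedules CTCAE v5 at inclusion, at the end of radiotherapy and at every follow-up visit, and records SAEs and survival status at every follow-up visit. No trigger based on SAEs is stated.

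**The concern.** A safety count should not leave out the most serious outcomes. Here both statements of the rule name grade 3 alone, in an article that uses the ≥ sign elsewhere, and nothing in the text brings grade 4 or 5 events into the 5% comparison.

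The comparison acts as a gate, because the p < 0.001 test is run only if it is passed. Events outside the count cannot open it. The look is meant to catch unexpected harm from a schedule for which the article itself calls the salvage data scarce, yet an excess made up of grade 4-5 events would be the one least likely to be flagged.

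This is not a detail left to a fuller document. The article fixes the grade, the threshold, the timing and the significance level.

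**Working it through.** **Inputs.** Total sample size 538 ("we need to recruit 269 participants per treatment arm: 538 in total"), interim fraction 25%, 1:1 allocation and a trigger above 5%, read as percentage points. Assumptions: 68 experimental and 67 control participants at the look, and all event rates below, since the documents give none.

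**1. The plan's own figure.** 0.25 × 538 = 134.5, which rounds up to the stated 135.

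**2. What meets the trigger.** Find the smallest experimental count e, for control count c, with e/68 − c/67 > 0.05:

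| Control | Experimental needed | Difference |
|---|---|---|
| 0 | 4 | 4/68 − 0 = 5.88 points |
| 1 | 5 | 5/68 − 1/67 = 7.35 − 1.49 = 5.86 points |
| 2 | 6 | 6/68 − 2/67 = 5.84 points |
| 3 | 7 | 7/68 − 3/67 = 5.82 points |

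**3. Events recorded only at grade 4 or 5.**

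- Four such experimental cases against none: 0/68 − 0/67 = 0 under grade 3, and 5.88 points under grade ≥ 3 (trigger met).
- Three grade 3 and three grade 4 experimental cases against one grade 3 control: 3/68 − 1/67 = 2.92 points under grade 3 (not met), and 6/68 − 1/67 = 7.33 points under grade ≥ 3 (met).

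**4. Worsening from grade 3 to grade 4.** This step applies only if participants are counted by highest grade. Start at 5 against 1, which is 5.86 points and meets the trigger. If one experimental participant worsens to grade 4, the count is 4 against 1: 4/68 − 1/67 = 5.88 − 1.49 = 4.39 points, not met. Under grade ≥ 3 the difference stays at 5.86. If anyone who ever had a grade 3 event is counted, worsening changes nothing, but the cases in step 3 are still missed.

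**5. Probability of triggering.** With independent binomial counts C (n = 67) and E (n = 68), sum P(C = c) × P(E = e) over all pairs with e/68 − c/67 > 0.05. The control rate is held fixed, and only the experimental arm's mix of grades changes.

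| Assumed grade ≥ 3 rate, experimental vs control | Experimental points at grade 4-5 | Grade ≥ 3 rule | Grade 3 only |
|---|---|---|---|
| 8% vs 1% | 0 | 69% | 69% |
| 8% vs 1% | 2 | 69% | 46% |
| 8% vs 1% | 4 | 69% | 20% |
| 8% vs 1% | 6 | 69% | 3% |
| 10% vs 2% | 0 | 76% | 76% |
| 10% vs 2% | 3 | 76% | 47% |
| 10% vs 2% | 5 | 76% | 24% |

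The two rules coincide when no event goes beyond grade 3. They separate as the mix becomes more severe.

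**6. The test behind the gate.** The documents name no test, so Fisher's exact test is assumed. Four against none gives p = 0.12. Reaching p < 0.001 needs at least 11 against 0 (11/68 = 16.2 points) or 14 against 1.

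**The case against.** The best defence is that grade 3 is shorthand for grade 3 or worse. That fits the stated purpose, and a journal article condenses its parent protocol. A reader might infer from the wording that the trial has deliberately excluded grade 4 and 5 events. The article does not show that; it shows only that the rule as written does not include them. The shorthand reading does not make the correction unnecessary, since the independent statistician should not have to choose a reading once arm-level data are visible.

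Four further readings go beyond the text.

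- **That worsening necessarily lowers the signal.** This needs a highest-grade count, which the article states for the main toxicity comparison but not for the interim look.
- **That severe events would go unseen.** SAEs, survival status and CTCAE grades are all collected, and the principal investigators judge whether it is safe to continue after informing the ethics committee. What is missing is a stated route from grade 4-5 events into the quantitative trigger.
- **That the wording would change a decision to continue.** In the example of four against none, counting the events would start the formal test but come nowhere near its boundary (p = 0.12).
- **That the rule should be restricted to GI and GU events to match the secondary endpoint.** A rule that counts any organ is broader, which is no fault in a safety screen. Narrowing it would remove events that now count.

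It is also fair to say that the examples are constructed, and that the two definitions nearly coincide if grade 4-5 acute events are very rare. That limits the expected size of the effect. It does not justify the wording, because the look is aimed at toxicity that was not expected.

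**Conclusion.** The concern holds as a defect in the wording of a stated rule. Taken literally, the gate ignores participants recorded only at grade 4 or 5, and no other text in the article repairs this.

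Its size depends on the grade 4-5 rate, which the documents do not give. Under the assumed rates, the loss in triggering probability runs from nothing (no grade 4-5 events) to 66 percentage points (69% to 3%, when 6 of 8 points are grade 4-5). The loss on worsening, 5.86 to 4.39 points in the example, is conditional on counting by highest grade.

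The effect is on whether the formal test is opened, not on the p < 0.001 boundary. The conclusion rests on the literal reading, a 68/67 split and the 5% being percentage points.

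**What to change.** In both places in the Interim analysis section, replace the grade 3 wording with: grade ≥ 3 CTCAE acute toxicity (highest grade per participant). With that wording, a highest-grade count and an ever-reached count give the same number, so the question about worsening disappears as well. Leave the organ scope as it is; this change should not narrow it to GI and GU.

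The cost is a short amendment. No new data are needed, because CTCAE v5 is already scored at inclusion, at the end of radiotherapy and at each follow-up visit. The wording should be settled before arm-level toxicity is examined. If the look has already taken place, report which reading was applied and give the counts under both.

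### The toxicity interim screens at a 5-point excess but calls it significant only at p < 0.001, which needs an observed excess of about 16 points

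*Protocol article*

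**What the plan says.** All of this stands in the Interim analysis section of the protocol article.

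- Timing: the look comes "after the inclusion of 25% of the estimated number of participants (135 participants". Allocation is 1:1 (Abstract, Methods: "Participants will be randomised in a 1:1 ratio"), so the arms hold about 67 and 68.
- Step 1, a descriptive screen that compares the arms: "Grade 3 CTCAE acute toxicity will be used for this interim analysis; i.e., > 5% difference in grade 3 toxicity".
- Step 2, conditional on step 1: "If this acute toxicity difference exceeds 5%, a formal interim analysis will be performed". The threshold set for this second step is a p "value < 0.001 according to the Haybittle-Peto alpha spending function, to indicate statistical significance". The article does not say whether this is one- or two-sided, nor which test is used.
- Purpose and decision: the aim is to pick up early signs of excessive acute toxicity. An independent statistician does the analysis. The principal investigators judge whether it is safe to continue, after informing the ethical committee.

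The section expects equivalent toxicity, but allows that acute toxicity might be slightly higher in the experimental arm. It gives no expected grade 3 rate and no power for this look.

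**The concern.** A Haybittle-Peto boundary is strict at interim looks so that the final test of the same hypothesis keeps nearly all of its alpha. Here the interim tests acute toxicity, whereas the primary endpoint is 5-year PFS. No PFS alpha is spent, so the strict level has nothing to protect. Its only effect is to make the formal criterion insensitive to harm, in a look whose stated purpose is to find harm.

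What is at stake is the information passed on. Those who judge continuation would receive a formal result that is very unlikely to be significant at the size of excess the plan itself singles out, and unlikely even at two or three times that size.

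**Working it through.** **Interim size.** 0.25 × 538 = 134.5, which reproduces the stated 135. At 1:1 this is taken as 67 control and 68 experimental.

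**Assumption.** The control grade 3 rate is not in the article. I use 2%, 3% and 5%.

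**Smallest significant result.** Pooled z = (pE − pC) / √[p(1−p)(1/67 + 1/68)], with p the pooled proportion. Two-sided p < 0.001 needs z > 3.29.

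- 0/67 v 10/68: p = 0.0741, SE = 0.0451, z = 0.1471/0.0451 = 3.26. Not significant.
- 0/67 v 11/68: p = 0.0815, SE = 0.0471, z = 0.1618/0.0471 = 3.44. Significant.

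Fisher's exact test gives the same minimum (p = 0.0014 at 10 events, 0.0006 at 11). With more control events the gap widens:

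| Control events (of 67) | Smallest experimental count passing the >5-point screen (of 68) | Smallest count with two-sided p < 0.001, z / Fisher | Excess needed, points |
|---|---|---|---|
| 0 | 4 | 11 / 11 | 16 |
| 1 | 5 | 13 / 14 | 18-19 |
| 2 | 6 | 15 / 16 | 19-21 |
| 3 | 7 | 17 / 18 | 21-22 |

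Read one-sided, the minimum with no control events falls only to 10/68, or 15 points.

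**Operating characteristics.** I summed the binomial probabilities of all outcomes at 67 v 68 in which the observed excess is above 5 points and, for step 2, p < 0.001 as well. Ranges cover control rates of 2-5%; step 2 also spans the z and Fisher tests, two-sided.

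| True excess | Step 1 screen fires | Steps 1 and 2: p < 0.001 |
|---|---|---|
| 0 points | 2-8% | below 0.1% |
| 5 points | 47-49% | 0.2-0.5% |
| 10 points | 84-88% | 4-7% |
| 15 points | 97-98% | 18-34% |

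One-sided p < 0.001 gives 0.5-1.0% for a 5-point excess. Widening the control rate to 0.5-10% leaves the two-sided figure for 5 points at 0.1-0.5%.

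**Sample size that p < 0.001 would need.** By the normal approximation, 80% power takes about 460 per arm for 1% v 6% and 946 per arm for 5% v 10%. The whole trial has 269 per arm.

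**A lenient test for comparison.** One-sided 0.10 with the screen kept:

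| True excess | z test | Fisher |
|---|---|---|
| 0 points (false alarm) | 2-8% | 1-4% |
| 5 points | 44-47% | 30-36% |
| 10 points | 77-87% | 66-78% |

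The z test at 0.10 has the same minimum counts as the screen when the control arm has 0 to 3 events, so it adds little to step 1. The gain comes from removing p < 0.001.

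**The case against.** A reader might infer that the interim almost never picks up a 5-point excess. The article does not support that. Step 1 is the part aimed at 5 points, and it fires about half the time when the true excess is 5 points and over 80% of the time at 10. What almost never happens at 5 points is the formal label of significance.

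A reader might also treat p < 0.001 as a stopping rule under which a non-significant result means carry on. The text says neither. The threshold only indicates significance, and the decision rests on judgement. Those who judge would see a formal analysis only because the difference had already passed 5%. CTCAE and SAE data are also collected at each follow-up visit (Table 3). All of this stands, and it lowers the severity. It does not give the strict level a purpose.

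Two side points are weaker than they look:

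- **Grade.** The section says "Grade 3 CTCAE acute toxicity will be used for this interim analysis", while the Secondary endpoints section writes grade ≥ 2 for its toxicity outcomes. Read literally, grade 4 and 5 events would not count. This may be shorthand in a condensed article, and such events would still reach SAE reporting.
- **Timing.** A reader might infer that much of the data would be immature, since acute toxicity is measured 3 months after treatment and treatment lasts 4 or 7 weeks. But inclusion of 135 may define the cohort rather than the date of the data cut. Any percentage would need an accrual rate and a wait before radiotherapy that the article does not give.

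**Conclusion.** The concern holds as a mismatch between the two steps. The plan singles out a 5-point difference, then attaches a significance criterion that cannot be met below an observed excess of about 16 points two-sided (15 one-sided). A true 10-point excess would miss p < 0.001 93-96% of the time and a 15-point excess 66-82% of the time, so a non-significant result says little about safety.

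The minimum counts depend only on the 67/68 split, the test and its sidedness. The probabilities also rest on assumed control rates of 2-5%, but the figure for a 5-point excess stays at or below about 1% for any control rate from 0.5% to 10%, either sidedness and either test. Fewer evaluable participants at the look would lower power further.

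This should be fixed but is not critical: the rule does not bind, the descriptive screen is reasonably sensitive, and the PFS analysis is untouched. Grade wording and timing are secondary clarifications.

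**What to change.** In the Interim analysis section:

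1. Delete the p < 0.001 Haybittle-Peto criterion, and state that the look tests toxicity only and spends no PFS alpha.
2. Let the >5-point screen itself trigger the report to those who judge continuation, with the counts per arm, the estimated difference and its confidence interval.
3. If a test is wanted, name it and its direction, and set a lenient level. One-sided 0.10 is one example: about 30-47% for a true 5-point excess and 66-87% for 10 points, depending on Fisher or z test.
4. Secondary wording: write grade ≥3, and base the look on the first 135 participants once their acute-toxicity assessment to 3 months is complete.

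The cost is one paragraph of text and no extra participants. With equal true rates of 2-5%, a lenient test raises a false alarm 1-8% of the time and the screen alone 2-8%; each prompts a review. If the data cut was meant to fall at the 135th inclusion, the look comes some months later.
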